### 2.3. Recruitment and Randomization of Study Participants

Participants will be recruited during the pre-admission dietary visit, 2–3 weeks prior to surgery. The screening procedure will only require routine/daily practice examinations to check that the patient meets the inclusion and exclusion criteria. In particular, screening for inclusion and exclusion criteria will be based on the patient’s clinical history, home medication, routine pre-admission laboratory tests, dietary intake, and presence/absence of caregivers in the case of dependent or elderly patients. No payment or compensation will be provided to study participants. After signing the informed consent form, eligible participants will be randomised 1:1 by the treating physician to one of the two study arms according to a computer-generated random block randomisation list. Randomisation will be stratified by centre.

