The key secondary objective is to compare preoperative IMN with standard ONS in terms of the rate of severe complications (i.e., Clavien–Dindo grade ≥ III) in the first 30 days after RC. The other secondary objectives of the study are as follows:To compare preoperative IMN with standard ONS in terms of the rate of severe complications in the first 90 days after RC;To compare preoperative IMN with standard ONS in terms of the rate of infectious complications in the first 30 and 90 days after RC;To compare preoperative IMN with standard ONS in terms of the rate of occurrence of other medical conditions in the first 30 and 90 days after RC;To compare preoperative IMN with standard ONS in terms of time to recovery of bowel function, defined as the time from surgery to first flatus;To compare preoperative IMN with standard ONS in terms of time to postoperative mobilization, defined as the time from surgery to first walk;To compare preoperative IMN with standard ONS in terms of changes in muscle strength, defined as the difference in hand-grip strength (mean of three consecutive measurements from the dominant hand) and in the sit-and-stand test from the preadmission visit to the day before surgery to hospital discharge;To compare preoperative IMN with standard ONS in terms of weight modifications, defined as the difference in body weight from the preadmission visit to the day before surgery to hospital discharge to the 90-day follow-up visit;To compare preoperative IMN with standard ONS in terms of biochemical nutritional index modifications, i.e., changes in haemoglobin, lymphocytes, albumin, prealbumin, C-reactive protein, cholinesterase, total cholesterol, glucose, and creatinine, from the preadmission visit to the day before surgery to hospital discharge;To compare preoperative IMN with standard ONS in terms of the need for blood transfusions, defined as the percentage of patients who receive blood transfusions during their hospital stay;To compare preoperative IMN with standard ONS in terms of length of stay (LOS), defined as the time from hospital admission to discharge at home or to another facility;To compare preoperative IMN with standard ONS in terms of 30-day and 90-day readmission rate, defined as the incidence of unplanned re-hospitalization due to all causes in the first 30 and 90 days;To compare preoperative IMN with standard ONS in terms of 30-day and 90-day mortality, defined as death rate due to all causes during the first 30 and 90 days post-surgery;To compare the compliance to preoperative IMN and standard ONS, defined as the percentage of patients consuming ≥ 80% of the prescribed supplement in the 7 days before surgery;To compare the tolerability of preoperative IMN and standard ONS, defined as the percentage of patients experiencing at least one moderate–severe adverse gastrointestinal effects during the 7-day intervention period;To compare preoperative IMN with standard ONS for the primary endpoint and the key secondary endpoint in the subgroups of the following:

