### 2.6. Data Collection Methods

Data will be collected at five time points: during the screening visit, at hospital admission, at hospital discharge, at 30 days after surgery (by telephone), and 90 days after surgery.

Screening visit. The screening visit takes place during the pre-admission visit by the referring dietitian/nutritional biologist, usually 14–28 days before surgery. After evaluation of the inclusion and exclusion criteria and signing of informed consent, the following data will be collected: demographics; medical history and medications; laboratory data; pregnancy test in women of childbearing potential; anthropometric parameters; nutritional risk according to NRS-2002; body composition via analysis of basal CT scan images (if performed in the two months prior to the preadmission visit); muscular strength by digital hand-grip dynamometer and sit-and-stand test.Hospital admission. Hospital admission is usually the day before surgery. The following data will be recorded: anthropometric parameters; muscular strength as described above; compliance based on the number of servings of supplements consumed by the patient; tolerability measured using a questionnaire.Hospital discharge. Hospital discharge is usually 15 to 20 days after surgery. The following data will be recorded: anthropometric parameters; muscle strength as above; type of urinary reconstruction; day of recovery of bowel function; day of discontinuation of systemic/peridural opioid analgesic therapy, if any; day of removal of naso-gastric tube, if any; use of parenteral nutrition and/or ONS after surgery; blood transfusions performed during hospital stay; need for ICU stay; vital status.Thirty days after surgery. A follow-up telephone call will be made 30 days after surgery. The following data will be collected, if available: postoperative complications and other medical conditions; re-hospitalisation; vital status. If patients are still hospitalised 30 days after surgery, data will be collected during hospitalisation.Ninety days after surgery. A follow-up visit will be performed ninety days after surgery. The following data will be collected, if available: anthropometric parameters; postoperative complications and other medical conditions; re-hospitalisation; initiation of adjuvant chemotherapy; vital status. If patients are still hospitalised 90 days after surgery, data will be collected during hospitalisation.

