#### 2.7.2. Planned Analyses

The main analysis will be conducted according to the intention-to-treat (ITT) principle: patients in the analysis set will be analysed according to the treatment to which they were randomised, regardless of the treatment actually received. The ITT population will be used for the primary and secondary endpoints. Per-protocol (PP) analyses will also be performed, taking into account the treatment actually received. Specifically, per-protocol analyses will compare compliant patients in the IMN group with compliant patients in the control group for the primary and key secondary endpoints. The safety population will include all patients who consume at least one dose of the assigned treatment and will be used for the safety analyses. The two-sided type I error will be set at 5% (adjusting for Bonferroni’s correction when necessary). All statistical analyses will be performed using Stata 18 (StataCorp. 2021. Stata Statistical Software: Release 18. College Station, TX, USA: StataCorp LLC.)

The primary objective will be analysed using a binomial regression model, with link identity. The risk difference and its 95% confidence interval (95%CI) will be derived from the model. Huber–White robust standard errors will be used while clustering on centre to account for the lack of independence within centre.

The statistical analysis for the key secondary objective and for several other secondary objectives (no. 9, 13, and 14) will be performed in the same way as the primary objective. Other secondary objectives will be analysed using a time-to-event analysis (no. 1–5 and 10–12) or with Mann–Whitney U test (no. 6–8). Effect modification by subgroup will be assessed by introducing the interaction of subgroup and treatment in the corresponding statistical model (no. 15).

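### Objectives 6–8 (changes in strength, weight and laboratory markers) are assigned an unadjusted Mann–Whitney test: valid, but less powerful than adjusting for baseline and centre

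*Protocol article*

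**What the plan says.** Section 2.7.2 (Planned Analyses) allocates methods to the secondary objectives by number: "Other secondary objectives will be analysed using a time-to-event analysis (no. 1–5 and 10–12) or with Mann–Whitney U test (no. 6–8"). The list in section 2.5 is not numbered in the text. Counting from the first item after the key secondary objective gives strength as 6, weight as 7 and biochemistry as 8. The count fits the rest of section 2.7.2: numbers 9, 13 and 14 fall on the percentages that are analysed like the primary endpoint, and number 15 falls on the subgroups.

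All three objectives are defined as changes:

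- Strength: "changes in muscle strength, defined as the difference in hand-grip strength (mean of three consecutive measurements from the dominant hand"), together with the sit-and-stand test, over three time points (preadmission visit, day before surgery, discharge).
- Weight: "the difference in body weight from the preadmission visit to the day before surgery to hospital discharge to the 90-day follow-up visit", which is four time points.
- Laboratory markers: "biochemical nutritional index modifications, i.e., changes in haemoglobin, lymphocytes, albumin, prealbumin, C-reactive protein, cholinesterase, total cholesterol, glucose, and creatinine", nine markers over the same three time points as strength.

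The baseline is collected. The screening visit in section 2.6 records "muscular strength by digital hand-grip dynamometer and sit-and-stand test", and the same list includes laboratory data and anthropometric parameters. Section 2.3 adds: "Randomisation will be stratified by centre". There are two centres.

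For the primary endpoint, section 2.7.2 specifies a model-based risk difference with a 95% confidence interval and standard errors clustered on centre. For objectives 6–8 it names the test and nothing further.

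**The concern.** These outcomes are continuous and have a pre-treatment value, and randomisation is stratified by centre. Both pieces of information can be used at no cost in data. The standard two-sample Mann–Whitney test accepts neither a covariate nor a stratum.

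Subtracting the baseline is not the same as adjusting for it. Subtraction fixes the slope of follow-up on baseline at 1. When the true slope is lower, the change score carries baseline noise that ANCOVA would remove. If the two centres also differ in how much patients change, that difference stays in the unstratified test as extra noise.

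At stake is the power to detect a difference in strength, weight or laboratory markers. A real effect could be missed for a reason that has nothing to do with sample size. Because the method is named, this is a stated choice and not a detail left open for the analysis plan.

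**Working it through.** **1. The plan's own figure.** The only sample size stated is for the primary endpoint (section 2.7.1): 72% against 55%, two-sided 5%, 80% power. With the pooled mean (0.72 + 0.55)/2 = 0.635:

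n = [1.960·√(2·0.635·0.365) + 0.8416·√(0.72·0.28 + 0.55·0.45)]² / 0.17² = (1.334 + 0.564)² / 0.0289 ≈ 124.7, so 125 per arm.

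The stated 125 is reproduced. It does not bear on objectives 6–8 except as a plausible number of patients per arm. The document gives no standard deviation, correlation or target difference for these objectives.

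**2. Relative efficiency.** Let ρ be the correlation between baseline and follow-up, with equal standard deviation σ at both times.

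- Variance of a change score: 2(1 − ρ)σ².
- Residual variance under ANCOVA: (1 − ρ²)σ².
- Ratio, ANCOVA to change score: (1 + ρ)/2.
- Asymptotic efficiency of Mann–Whitney relative to a comparison of means, under normality: 3/π = 0.955.
- Combined efficiency of Mann–Whitney on changes relative to ANCOVA: E = (3/π)(1 + ρ)/2.

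**3. Power.** Set the effect so that ANCOVA has 80% power, which puts its standardised effect at 1.960 + 0.8416 = 2.802. The power of Mann–Whitney on changes is then Φ(2.802·√E − 1.960). For ρ = 0.5, E = 0.955 × 0.75 = 0.716, √E = 0.846, and Φ(2.371 − 1.960) = 0.66. The number per arm cancels in this step. It enters only in the last column, 125 × E, the number with which ANCOVA would match Mann–Whitney at 125.

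| Assumed ρ | (1 + ρ)/2 | Mann–Whitney power when ANCOVA has 80% | ANCOVA number per arm matching Mann–Whitney at 125 |
|---|---|---|---|
| 0.3 | 0.65 | 60% | 78 |
| 0.5 | 0.75 | 66% | 90 |
| 0.7 | 0.85 | 71% | 102 |
| 0.8 | 0.90 | 74% | 107 |
| 0.9 | 0.95 | 76% | 113 |
| 0.95 | 0.975 | 77% | 116 |

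**4. Simulation.** This used 125 per arm, two centres balanced between arms, normal data and 3,000 runs per setting. ANCOVA included baseline and centre. The centre shift of 0.5 SD in change is an assumption.

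| ρ | Centre shift | Power, Mann–Whitney | Power, ANCOVA | Type I error, Mann–Whitney |
|---|---|---|---|---|
| 0.5 | none | 65% | 78% | 5.3% |
| 0.7 | none | 71% | 79% | 5.3% |
| 0.9 | none | 75% | 79% | 4.7% |
| 0.5 | 0.5 SD | 64% | 80% | 4.2% |
| 0.7 | 0.5 SD | 68% | 80% | 3.1% |
| 0.9 | 0.5 SD | 65% | 79% | 2.7% |

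Without a centre shift the simulation agrees with the formula. With one, Mann–Whitney becomes conservative. Its power then falls even at high ρ, where baseline adjustment alone would add little.

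**The case against.** The strongest defence is that a pre-specified rank test on changes is legitimate. It needs no distributional assumption, avoids choosing a transformation for nine analytes, and can match or beat an untransformed linear model for a skewed marker such as C-reactive protein. The objectives are non-key secondary ones, and the trial is sized on the primary endpoint alone. All of this stands, and it limits the weight of the point.

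Four stronger readings are tempting, and the document does not support them.

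- *The baseline is thrown away.* It is not: section 2.5 defines each outcome as a change, so the preadmission value is subtracted. What is missing is its use as a covariate.
- *The comparison is biased or yields false positives.* Under randomisation a baseline imbalance is chance, and its effect is the variance loss already counted above. Type I error was nominal, or conservative where centres differ.
- *The plan will report only p-values, or will test each interval separately.* Section 2.7.2 is silent on both. Medians by arm or a Hodges–Lehmann shift with an interval would fit its wording and may be in the analysis plan, which is not shown. Silence in a condensed article is no defect.
- *The ratio (1 + ρ)/2 alone gives the cost of the plan.* That ratio compares ANCOVA with a mean-based analysis of changes. The planned test is Mann–Whitney, so the factor 3/π belongs in the calculation. No single figure fits all three objectives, since ρ will differ among them.

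**Conclusion.** The point holds as a loss of efficiency on non-key secondary outcomes. For an effect that ANCOVA with baseline and centre detects with 80% power, Mann–Whitney on changes has about 60% to 77% power over assumed correlations of 0.3 to 0.95. The loss is material for weakly correlated measures and small for strongly correlated ones, probably including body weight, unless the centres differ in how much patients change.

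These sizes rest on normality, equal standard deviations at baseline and follow-up, and assumed correlations. For skewed analytes they apply, at best, on a transformed scale. The planned test itself is valid, and the primary and key secondary analyses are untouched. The change is worth making because it needs no further data.

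**What to change.** For objectives 6–8, make the main analysis a regression of the follow-up value on arm, baseline value and centre. Where there are several follow-up times, use a mixed model with arm-by-visit terms. Take the preadmission value as baseline throughout, because the day-before-surgery value is measured after the supplement has been taken. Log-transform skewed analytes such as C-reactive protein. Report the adjusted difference, or the ratio for logged analytes, with a 95% confidence interval. Keep a rank test as a sensitivity analysis, preferably stratified by centre (van Elteren).

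The cost is wording in the analysis plan and slightly more analysis work. The downside is that the models bring assumptions which the rank test avoids. The model form and the list of analytes to be transformed must therefore be fixed before the data are seen by arm. No new visits, measurements or patients are needed.

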## 3. Discussion

Several studies have investigated the role of perioperative IMN in patients with bladder cancer undergoing surgery. Data are scarce, mainly due to the small sample sizes of these studies [23]. Moreover, some trials show controversial results. Nevertheless, the few available studies suggest a potential beneficial effect of IMN in this context [17].

Bertrand and colleagues were the first to evaluate the use of preoperative IMN (preoperative 7-day administration, 3 doses per day) in patients undergoing RC for BC with a retrospective case–control study; the authors observed a 48% relative reduction in the 30-day complication rate (40 vs. 76.7%) and lower rates of paralytic ileus at postoperative day 7 compared with patients who did not receive IMN [20]. Lyon and colleagues reported no improvement in the 90-day complication rate in patients treated with IMN (5-day preoperative administration, 4 doses per day) compared with no IMN [24]. Similarly, in a retrospective study, Cozzi and colleagues did not report lower rates of postoperative complications in RC candidates treated with perioperative IMN (7-day preoperative administration, 3 doses per day, and 7-day postoperative administration, 2 doses per day) [25]. However, Khaleel and colleagues retrospectively described a reduction in postoperative TPN requirements and infectious complication rates (25 vs. 45%) with IMN (5-day administration, 1 dose per day) [21]. The impact of IMN in the context of the ERAS protocol was recently evaluated in a case–control study comparing a historical cohort with IMN (5-day preoperative administration, 3 doses per day) in conjunction with preoperative carbohydrate load according to the ERAS protocol; no differences in complication and re-admission rates were detected [22].

Very few studies have compared IMN with standard ONS. Hamilton-Reeves and colleagues found that perioperative IMN versus standard ONS was associated with a 33% relative reduction in the postoperative complication rate and a 39% reduction in the infection rate during late-phase recovery, whereas no difference was found in the first 30 days (71% vs. 73%). In addition, lower levels of total myeloid-derived suppressor cells and plasma IL-6 were found on postoperative day 2 [19]. The same group reported a favourable shift in the Th1-Th2 balance from baseline to the intraoperative period and a trend towards less profound muscle loss in patients receiving IMN compared to standard ONS at postoperative day 14 [26]. A randomised phase III double-blind clinical trial is currently investigating the role of perioperative IMN with a novel supplement containing arginine, omega-3 fatty acids, nucleotides, and vitamin A in patients undergoing RC [27].

Of note, several aspects remain largely unclear, including the dosage and timing of IMN within enhanced recovery pathways and the impact of preoperative malnutrition risk on IMN efficacy.

## 4. Conclusions

Our study will help to clarify the impact of preoperative IMN in patients undergoing RC for BC. If successful, there is potential for preoperative IMN to become the standard of care for patients undergoing RC. In addition, the results of this study may provide new insights into the impact of malnutrition on postoperative outcomes and may help to improve IMN prescribing based on nutritional status parameters. Furthermore, our study on patients undergoing RC for BC may provide valuable information for investigating the role of preoperative IMN in other urinary surgeries, including nephrectomy or radical prostatectomy.

## Figures and Tables

**Table 1 healthcare-12-00696-t001:** Complications and other postoperative medical conditions evaluated in the study.

Complications	
Infectious complications	Abdominal abscess Bloodstream infection *C. difficile* colitis Cholecystitis Diverticulitis Pneumonia Pyelonephritis Wound infection with systemic signs
Gastrointestinal complications	Anastomotic bowel leak/fistula Functional ileus Gastrointestinal bleeding requiring transfusion Small bowel obstruction
Wound-related complications	Hernia or evisceration Wound dehiscence Wound infection without systemic signs
Genito-urinary complications	Urinary bleeding requiring transfusion Symptomatic lymphocele Ureteral obstruction Urinary fistula/leak
**Other Medical Conditions**	
Cardio-pulmonary complications	Congestive heart failure Myocardial infarction New onset of arrhythmia Pleural effusion requiring drainage
Thrombotic complications	Deep venous thrombosis Peripheral arterial ischemia Pulmonary embolism
Neurologic complications	Intracranial haemorrhage Delirium requiring psychiatric therapy Stroke Transient ischemic attack
Miscellaneous	Hyperglycaemia requiring insulin therapy in non-diabetic patients New onset of pressure ulcers Other

## Data Availability

No new data were created or analyzed in this study. Data sharing is not applicable to this article.
